# pseudocode for feature selection and modeling
import numpy as np
import pandas as pd
from sklearn.pipeline import make_pipeline
from sklearn.model_selection import GridSearchCV, StratifiedKFold
from sksurv.linear_model import CoxnetSurvivalAnalysis
# Define a function to generate alpha values using CoxnetSurvivalAnalysis
def get_alpha(l1, x, y):
    c_p = make_pipeline(
        CoxnetSurvivalAnalysis(l1_ratio=l1, alpha_min_ratio=0.00001, max_iter=1000)
    )
    c_p.fit(x, y)
    return c_p.named_steps["coxnetsurvivalanalysis"].alphas_
# Define a function to build a single-layer survival analysis pipeline
def build_pipeline(l1, idx, x, y):
    X_cov = x.loc[:, idx]
    # Initialize StratifiedKFold with the event indicator for stratification
    skf = StratifiedKFold(n_splits=10, shuffle=True, random_state=0)
    # Generate candidate alpha values using the get_alpha function
    candidate_alphas = get_alpha(l1, X_cov, y)
    # Prepare parameter grid for GridSearchCV; wrap each alpha in a list
    param_grid = {"coxnetsurvivalanalysis__alphas": [[v] for v in candidate_alphas]}
    # Set up GridSearchCV with the CoxnetSurvivalAnalysis model in a pipeline
    pipeline = GridSearchCV(
        make_pipeline(CoxnetSurvivalAnalysis(l1_ratio=l1)),
        param_grid=param_grid,
        cv=skf.split(X_cov, y["event"])
    )
    return pipeline

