### **3.7 Statistical Analysis**

The APOL1–high-risk cohort will be randomly divided into an 80% training set and 20% test set (stratified by outcome incidence). In the training set, candidate proteins will be selected via an elastic-net penalized Cox proportional hazards regression (age, sex, baseline eGFR, and log2(UACR) included as unpenalized covariates). Tuning parameters ( $\alpha$ ,  $\lambda$ ) will be chosen by 8-fold cross-validation. The final APRS model will include the nine selected proteins plus the four clinical covariates. Model discrimination will be quantified

by time-dependent AUC (tAUC) at prespecified time points and Harrell's C-index. Model performance will be compared to the KFRE (4-variable equation) and established CKD risk scores.

Proportional hazards assumptions for APRS and covariates will be tested using Schoenfeld residuals. Sensitivity analyses will address potential biases: we will apply inverse-probability-of-censoring weighting (IPCW) to account for informative loss-to-follow-up, computing weights within the training set. Feature stability will be assessed via bootstrap resampling. We will compute net benefit using decision-curve analysis (assuming equal weight for false positives and negatives). To gauge clinical utility, we will calculate the number needed to treat (NNT) to prevent one composite event under a hypothetical APOL1-targeted therapy: assuming a relative risk reduction of 27% (as reported for inaxaplin), NNT will be derived as the reciprocal of the absolute risk reduction. Comparisons of NNT between APRS-based risk stratification and standard models (KFRE) will be reported. All tests will be two-sided with  $\alpha=0.05$ .

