### **6.4.2 Regularized Cox Regression:**

We will perform a regularized Cox Regression where the L1/L2 ratio varies from 0 to 1. An alpha grid is automatically generated by sklearn and sksurv using 8-fold cross-validation, and the optimal alpha is selected based on the minimization of the partial likelihood deviance. Specifically, for a given L1 ratio, the model will be fitted using CoxnetSurvivalAnalysis (with an alpha\_min\_ratio set to 0.00001 and a maximum iteration of 1000), and a subset of alpha values is extracted for tuning. At each iteration we randomly sampled (with replacement) protein subsets drawn from the top 20% of proteins ranked by univariate AUC and fit the model on those subsets. This procedure was repeated across approximately 1 million different protein combinations.

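### SAP 6.4.2 and its pseudocode do not carry the unpenalised clinical covariates of protocol 3.7 into protein selection, and the pseudocode also departs from the stated tuning rule

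*Combined protocol and SAP*

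**What the plan says.** **Protocol 3.7.** The elastic-net Cox model that picks the candidate proteins has age, sex, baseline eGFR and log2(UACR) "included as unpenalized covariates". Its tuning parameters "will be chosen by 8-fold cross-validation". On the end product it says: "The final APRS model will include the nine selected proteins plus the four clinical covariates".

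**SAP 6.4.2.** The tuning rule is stated. The number of folds is 8, as in the protocol. For the criterion the section says: "the optimal alpha is selected based on the minimization of the partial likelihood deviance". The models are fitted to protein subsets "drawn from the top 20% of proteins ranked by univariate AUC and fit the model on those subsets", over about one million combinations. No clinical variable is named as part of the screen or of these fits.

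**SAP 6.4.3.** Clinical confounders are first mentioned when the APRS is generated, after the protein set has been chosen.

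**SAP pseudocode for feature selection and modelling (printed after 6.5).** The cross-validation object is set with "n_splits=10, shuffle=True, random_state=0". The estimator in the grid search is "make_pipeline(CoxnetSurvivalAnalysis(l1_ratio=l1", with no penalty factor and no scaling step, and the grid search has no scoring argument. Only the columns listed in `idx` enter. In the example call that is one feature, although the toy data also hold an age and an eGFR column.

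**The concern.** A programmer following the protocol and one following the SAP would run different selections. With the four covariates held in the model unpenalised, a protein is chosen for what it adds to them. With an unadjusted AUC screen followed by protein-only fits, a protein that tracks age, eGFR or albuminuria scores well whether or not it adds anything, and it takes a place that a protein with independent information could have had.

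This bears on a stated purpose of the study. SAP section 2 sets out to test the value of the proteins beyond genetic and clinical risk factors, and the final model contains the four covariates anyway. Proteins chosen partly as their proxies would be an inefficient use of the nine places.

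The tuning mismatch is a second, separate fault. The fold count and the scorer determine which penalty is chosen. They do not in themselves favour clinical proxies.

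**Working it through.** **1. The specifications side by side**

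| Item | Protocol 3.7 | SAP 6.4.2–6.4.3 text | SAP pseudocode |
|---|---|---|---|
| Clinical covariates in selection fits | four, unpenalised | none named; enter at score construction | none in the example; no penalty factor |
| Pre-screen | not described | top 20% by univariate AUC | not coded |
| Folds | 8 | 8 | 10 |
| Criterion for the penalty | cross-validation, criterion not named | minimum partial likelihood deviance | no scorer given |

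The protocol (3.2) gives 7,549 proteins, so the screen keeps 0.20 × 7,549 ≈ 1,510.

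**2. What the printed code does.** It was run as printed in scikit-survival 0.28.0.
- It uses 10 splits, so the stated figure of 8 is not reproduced.
- Scoring and penalty factor are both unset; one feature and one coefficient are fitted.
- The default score equals Harrell's C (0.6358 by both routes). The penalty is therefore chosen by concordance, not deviance.
- With the age and eGFR columns added to `idx`, both are penalised like a protein. At the largest penalty all three coefficients are 0.
- With penalty factors (1, 0, 0) at the same penalty, the two covariates stay in (0.011 and 0.023) and the protein is 0.

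**3. Can an unadjusted screen favour proxies?** The simulation used 680 people and 17.8% events, matching the 121 of 680 in Supplementary Table 1. It compares one proxy protein with no effect of its own with one independent protein of HR 1.3 per SD, in 200 runs per row. The clinical HRs (per SD, each of age, eGFR and UACR) and the share of proxy variance that is clinical are assumptions; the documents give neither.

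| Clinical HR | Proxy variance clinical | Proxy \|z\|>1.96, unadjusted | Same, adjusted | Proxy above independent on AUC | Same, on adjusted \|z\| |
|---|---|---|---|---|---|
| 1.2 | 25% | 43% | 5% | 23% | 4% |
| 1.2 | 50% | 64% | 7% | 30% | 5% |
| 1.4 | 25% | 90% | 5% | 64% | 5% |
| 1.4 | 50% | 99% | 3% | 84% | 3% |
| 1.6 | 25% | 98% | 6% | 84% | 4% |
| 1.6 | 50% | 100% | 6% | 98% | 4% |

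**4. What a whole screen would keep.** Again 680 people and 121 events, with assumed protein mixes.
- 300 proteins, top 60 kept; 60 or 120 proxies, 30 independent (HR 1.2), the rest noise; clinical HR 1.2–1.6; 25–50% of proxy variance clinical; 12 scenarios of 15 runs. With the AUC screen, 47–100% of kept proteins were proxies and 1–46% of independent proteins were recovered. With the adjusted screen, the figures were 13–34% and 61–66%.
- A similar design with 30 proxies, 30 independent and 240 noise proteins, clinical HR 1.6 and proxy correlation 0.5: recovery 50–75% unadjusted, 62–84% adjusted.
- The same with 120 proxies and clinical HR 2.5: unadjusted recovery 0%; no adjusted figure was recorded.

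**5. What the documents show about the nine proteins.** Supplementary Table 2 gives HRs adjusted for eGFR. Taking z = ln(HR)/SE, with SE = [ln(upper) − ln(lower)]/3.92, in the eGFR ≥60 column:
- MMP7: ln 1.86 = 0.621; SE = (0.833 − 0.412)/3.92 = 0.107; z = 5.8.
- WFDC2: ln 3.73 = 1.316; SE = (1.571 − 1.061)/3.92 = 0.130; z = 10.1.
- Across all nine, |z| runs from 5.8 to 10.1, and every interval excludes 1.

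**The case against.** The strongest reply has four parts.

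- **SAP 6.4.2 is silent, not contrary.** It describes how protein subsets are drawn and does not say that the covariates are left out. The protocol puts them in the same elastic net. This is fair, and it is why the point is an inconsistency to resolve and not proof of what was run. But the SAP is the document an analyst would program from, and it brings the clinical variables in only after selection.
- **The code is labelled pseudocode and runs on a toy example.** It has 50 random rows and one feature, with no AUC ranking and no subset loop. Covariates may have been passed through `idx` in the real run. This also stands: a reader might infer that the analysis itself penalised or dropped the covariates, and the documents do not establish that. The covariate gap, however, is in the SAP prose as well.
- **Supplementary Table 2.** A reader might infer that the chosen proteins merely stand in for clinical risk and would add little beside it. For eGFR, the only covariate the table adjusts for, the evidence is against that. Age, sex and UACR stay open. The HRs come from the same PMBB data after selection, and the table cannot show which independent proteins were passed over.
- **An adjusted pre-screen is not required by protocol 3.7,** and an inefficient screen does not by itself bias a later comparison of the finished score with clinical models. Both are correct. The adjusted screen is therefore a preference; the unpenalised covariates are the protocol's own rule.

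Nor does the SAP text omit the tuning rule. It states it, and only the pseudocode departs from it.

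**Conclusion.** The point holds as two separate faults.

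First, protocol 3.7 and SAP 6.4.2–6.4.3 describe different selections. Followed as written, the SAP may choose proteins partly as proxies for age, eGFR or UACR. In the simulations the direction was the same throughout, but the loss ranged from modest to total. It depends on the clinical effect sizes, on how many proteins track them and how closely, and the documents give none of these. In the weakest case the proxy usually ranked below the independent protein (it ranked above in 23% of runs). No single figure from these simulations should be quoted as the study's loss.

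Second, the pseudocode contradicts the stated tuning rule on folds (10 against 8) and criterion (concordance against deviance), and it has no means of leaving covariates unpenalised. This needs no assumption beyond the code as printed and the package's default score.

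The matter should be corrected. It does not show that the nine proteins are wrong.

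**What to change.** - Rewrite SAP 6.4.2 and the code to follow protocol 3.7: age, sex, baseline eGFR and log2(UACR) in every elastic-net fit with penalty factor 0.
- Standardise proteins within each training fold, use the stated 8 folds, and pass an explicit partial-likelihood-deviance scorer.
- Preferably, rank the pre-screen on association adjusted for the four covariates.
- Report the HRs of the nine proteins adjusted for all four covariates, alongside the eGFR-adjusted values in Supplementary Table 2.

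The data are already held, so the cost is a code change and a rerun of the subset search (about one million combinations). The protein list may change, and the results that depend on it would then have to be recomputed. If the covariates were in fact unpenalised in the analysis that was run, and tuning followed the stated rule, the remedy reduces to correcting the SAP text, printing the code actually used and adding the fully adjusted HRs.

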# ----- Example Data -----
np.random.seed(0)
n = 50 # number of samples
x_r = pd.DataFrame({
    "feature1": np.random.randn(n),
    "PC1": np.random.randn(n),
    "N264K": np.random.randn(n),
    "sp_age": np.random.randint(30, 70, n),
    "gfr": np.random.uniform(50, 100, n)
})
event = np.random.choice([True, False], n)
time = np.random.uniform(1, 10, n)
y_struct = np.array(list(zip(event, time)), dtype=[("event", bool), ("time", float)])
# Define idx as a list with one feature for the model
idx = ["feature1"]
l1 = 0.5
pipeline = build_pipeline(l1, idx, x_r, y_struct)
pipeline.fit(x_r.loc[:, idx].fillna(0), y_struct)
print("Best parameters:", pipeline.best_params_)
best_model = pipeline.best_estimator_.named_steps["coxnetsurvivalanalysis"]
print("Coefficients:", best_model.coef_)

```

## 7 Model Performance Evaluation

We will assess the predictive model using survival analysis metrics. The evaluation function takes as input the true survival outcomes (for both training and test sets), predicted risk scores, and the prediction time points. The process is as follows:

### 1. Data Preparation

Align predicted risk scores with true survival outcomes.

Apply inverse probability of censoring weights (IPCW) on the test set to adjust for censoring. The IPCW for sample  $i$  at time  $t$  is calculated as:  $IPCW_{i,t} = \frac{1}{\hat{S}(t|X_i)}$  where  $\hat{S}(t|X_i)$  is the estimated probability of being uncensored at time  $t$  given the covariates  $X_i$ .

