### 2. Metric Calculation at Each Time Point

Sort samples in descending order of risk scores.

For each time point  $t$ , define:

- **TP** (true positives)
- **FP** (false positives)
- **TN** (true negatives)
- **FN** (false negatives)

In the computation of these quantities, the IPCW is applied to the counts of events. For instance, the true positive count is computed as the sum of IPCW-adjusted indicators for cases (i.e., if an event occurs before or at time  $t$ ).

Compute performance metrics including:

- **AUC:**  $AUC_t = \int_0^1 TPR_t(FPR_t) dFPR_t$  where  $TPR_t$  is the true positive rate (sensitivity) and  $FPR_t$  is the false positive rate (1 - specificity) at time  $t$
- **Sensitivity:**  $Sensitivity_t = \frac{TP_t}{TP_t + FN_t}$
- **Specificity:**  $Specificity_t = \frac{TN_t}{TN_t + FP_t}$
- **F1 Score:**  $F1_t = \frac{2 \cdot Precision_t \cdot Recall_t}{Precision_t + Recall_t}$
- **Precision:**  $Precision_t = \frac{TP_t}{TP_t + FP_t}$
- **Accuracy:**  $Accuracy_t = \frac{TP_t + TN_t}{TP_t + FP_t + TN_t + FN_t}$
- **Recall:**  $Recall_t = \frac{TP_t}{TP_t + FN_t}$
- **Matthews Correlation Coefficient (MCC):**

$$MCC_t = \frac{((TP_t * TN_t) - (FP_t * FN_t))}{\sqrt{(TP_t + FP_t) * (TP_t + FN_t) * (TN_t + FP_t) * (TN_t + FN_t)}}$$

- **Positive Predictive Value (PPV) and Negative Predictive Value (NPV):**

$$PPV_t = \frac{TP_t}{TP_t + FP_t} \text{ and } NPV_t = \frac{TN_t}{TN_t + FN_t}$$

The binary classification threshold at each time point is chosen to maximize the sum of sensitivity and specificity.

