### 3. **Weighted Aggregation (for Multiple Time Points)**

If multiple time points are evaluated, compute the weighted mean of each metric using the survival probability at each time point

$$\bar{M} = \frac{\sum_{t=1}^m M_t \cdot \hat{S}(t)}{\sum_{t=1}^m \hat{S}(t)}$$

where  $M_t$  is the metric at time  $t$  and  $\hat{S}(t)$  is the estimated survival probability.

The function returns a dictionary containing the performance metrics at each time point, along with the overall weighted mean metrics if applicable. The pseudo code is as follows:

```

import numpy as np
from sksurv.util import check_y_survival
from sksurv.nonparametric import CensoringDistributionEstimator, SurvivalFunctionEstimator
def cum_metrics(survival_train, survival_test, estimate, times, AUC_sfd=False,
                tied_tol=1e-8):
    test_event, test_time = check_y_survival(survival_test)
    event_shuffle = test_event
    estimate, times = _check_estimate_2d(estimate, test_time, times,
                                         estimator="cumulative_dynamic_auc")

    n_samples = estimate.shape[0]
    n_times = times.shape[0]
    if estimate.ndim == 1:
        estimate = np.broadcast_to(estimate[:, np.newaxis], (n_samples, n_times))
    cens = CensoringDistributionEstimator()
    cens.fit(survival_train)
    ipcw = cens.predict_ipcw(survival_test)
    test_time = np.broadcast_to(test_time[:, np.newaxis], (n_samples, n_times))
    test_event = np.broadcast_to(test_event[:, np.newaxis], (n_samples, n_times))
    times_2d = np.broadcast_to(times, (n_samples, n_times))
    ipcw = np.broadcast_to(ipcw[:, np.newaxis], (n_samples, n_times))
    o = np.argsort(-estimate, axis=0)
    test_time = np.take_along_axis(test_time, o, axis=0)
    test_event = np.take_along_axis(test_event, o, axis=0)
    estimate = np.take_along_axis(estimate, o, axis=0)
    ipcw = np.take_along_axis(ipcw, o, axis=0)
    is_case = (test_time <= times_2d) & test_event
    is_control = test_time > times_2d
    n_controls = is_control.sum(axis=0)
    estimate_diff = np.concatenate((np.broadcast_to(np.infty, (1, n_times)),
                                   estimate))

    is_tied = np.absolute(np.diff(estimate_diff, axis=0)) <= tied_tol
    CU_tp = np.cumsum(is_case * ipcw, axis=0)
    CU_fp = np.cumsum(is_control, axis=0)
    CU_tn = n_controls - CU_fp
    CU_fn = CU_tp[-1] - CU_tp
    CU_n_neg = CU_tn + CU_fn
    CU_n_pos = CU_tp + CU_fp
    tpr_all = CU_tp / CU_tp[-1] # sensitivity

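### The SAP text sets the censoring weight at the horizon and the printed code sets it at each person's own event time; the text rule is invalid for earlier cases, and the code leaves controls unweighted

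*Combined protocol and SAP*

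**What the plan says.** SAP section 7, step 1 (Data Preparation) gives the weight two indices, person and time, and sets it to the reciprocal of S(t|X_i), where S "is the estimated probability of being uncensored at time" t given that person's covariates. Step 2 (Metric Calculation at Each Time Point) uses the same t for the evaluation time. It says that "the IPCW is applied to the counts of events", and that "the true positive count is computed as the sum of IPCW-adjusted indicators for cases" with an event before or at t. Read together, every case counted at horizon t carries the weight for horizon t.

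The `cum_metrics` code printed under step 3 works differently:

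- The censoring model is fitted to training outcomes only, with no covariates: "cens.fit(survival_train".
- The weight comes from each test person's own event and time record: "ipcw = cens.predict_ipcw(survival_test". No horizon is passed.
- That one weight is copied to every horizon: "ipcw = np.broadcast_to(ipcw[:, np.newaxis], (n_samples, n_times". It therefore cannot depend on t.
- Cases are weighted ("CU_tp = np.cumsum(is_case * ipcw, axis=0"), but the cumulative sums for false positives and true negatives count controls without any weight.

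Protocol section 3.7 agrees with the code on the fitting set ("computing weights within the training set") but does not say at which time the weight is evaluated.

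**The concern.** A case at year 2 had to stay uncensored only until year 2 to be seen. Its weight should be the reciprocal of the censoring survival at year 2, whatever the horizon. Weighting it as if it had to stay uncensored until year 9 over-counts it. Early cases are over-counted most, since their correct weights are closest to 1.

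Discrimination is a main claim of this study, and section 7 also promises PPV, NPV, precision, F1, accuracy and MCC. Anyone who implements the written formula gets different values from anyone who runs the code. The last six metrics also depend on the ratio of cases to controls, so unweighted controls matter for them even when the case weights are right.

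**Working it through.** The documents report no weighted case total, censoring curve or list of horizons, so there is no figure of theirs to reproduce. The sizes below rest on an assumed censoring curve.

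**Which weight is valid.** Let G be the probability of remaining uncensored, F and f the event distribution and density, and S = 1 − F.

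- Own-time weight: the expected weighted case fraction is ∫₀ᵗ f(u)G(u)/G(u) du = F(t), which is the target.
- Horizon weight: the expected fraction is [∫₀ᵗ f(u)G(u) du]/G(t). This exceeds F(t) because G(u) ≥ G(t) for u ≤ t.
- Controls: the observed fraction is S(t)G(t). A weight of 1/G(t) restores S(t); no weight leaves it too small.

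The scikit-survival routine called in the code returns the event indicator divided by G at the person's own time, so its case weights are of the first kind.

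**Inputs from the documents.** Derivation set of 851 with 153 events: 153/851 = 17.98% (SAP section 3). Median follow-up 7.3 years and mean time to event 6.51 years (SAP section 3). Follow-up 7.18 ± 2.89 years and time to event 6.51 ± 3.07 years (protocol Appendix 1). Truncation at 10 years (protocol section 3.6).

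**Assumptions.** Constant hazard 0.0276 per year and uniform censoring from a to b years, cut at 10. The three ranges used give 17.4–18.0% events, mean follow-up 7.0–7.3 years and median 7.5–7.6 years, close to the stated values. The SD, 2.3–2.8 years, is somewhat below the stated 2.89.

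**Worked case, a = 2, b = 13, t = 9.** F(9) = 1 − exp(−0.0276 × 9) = 0.220. G(9) = (13 − 9)/(13 − 2) = 0.364. The observed case fraction is ∫₀⁹ f(u)G(u) du = 0.169.

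- Text rule: 0.169/0.364 = 0.464, which is 2.1 times 0.220.
- Unweighted controls: 0.780 × 0.364 = 0.284.
- Case share with the code: 0.220/(0.220 + 0.284) = 0.44.
- Case share with the text rule: 0.464/(0.464 + 0.284) = 0.62.
- True share: 0.22.

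**All three ranges at 9 years.**

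| a–b (years) | G(9) | Text-rule case fraction | Ratio to 0.220 | Case share, code | Case share, text |
|---|---|---|---|---|---|
| 1.6–13.5 | 0.378 | 0.44 | 2.0 | 0.43 | 0.60 |
| 2–13 | 0.364 | 0.46 | 2.1 | 0.44 | 0.62 |
| 3–12 | 0.333 | 0.52 | 2.4 | 0.46 | 0.67 |

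At 5 years the text-rule fraction is 0.16 against 0.13 (ratio 1.23–1.27). At 7.3 years it is 0.29–0.30 against 0.18.

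**Other censoring shapes.** Weibull, uniform and beta censoring fitted to mean 6.51, SD 3.07 and 17.98% events give G(9) = 0.39–0.44. The ratio of text total to own-time total is then about 1.2 at 5 years and 1.6–2.1 at 9 years. With the 7.3-year median also imposed, the 9-year ratio is 1.8–1.9. For the 171-person test set this is about 31 observed cases by 9 years, about 38 with own-time weights and about 73 with horizon weights.

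**AUC.** Sensitivity is a ratio of weighted case sums. If all cases share the weight 1/G(t), it cancels and the AUC is the unweighted one. If the weight depends on X_i, it does not cancel. Simulated 9-year AUCs (400,000 people, illustrative score effects):

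| Setting | Truth | Unweighted | Text rule | Code |
|---|---|---|---|---|
| Censoring independent of score, constant effect | 0.838 | 0.844 | 0.844 | 0.838 |
| Censoring independent of score, fading effect | 0.752 | 0.787 | 0.787 | 0.753 |
| Censoring dependent on score (one example) | 0.839 | 0.875 | 0.918 | 0.867 |

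**The case against.** The strongest reply is that section 7 describes an evaluation function and then prints it. The printed function uses own-event-time weights, which recover the true AUC when censoring is independent of the score. Nothing in the documents shows that any metric was computed from the prose. This stands. A reader might infer that the reported AUCs are uncorrected for censoring; the documents do not support that. Even under the written rule, an unweighted AUC follows only if all cases share one weight, and the text conditions on X_i.

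The 9-year horizon is also not in the documents. Protocol section 3.7 refers only to prespecified time points, and SAP section 6.5 offers 5 or 10 years as examples for the NNT. At 5 years the inflation is modest. This stands too, so the result is given as a range over horizons.

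The AUC shifts depend on assumed score effects. With 32 events among 171 test participants, a Hanley–McNeil standard error at an AUC of 0.82 is near 0.05, larger than the shifts found under independent censoring (0.006 and 0.035). That limits the practical weight of the AUC shift, but sampling error does not make an invalid weight valid.

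One could also read t in step 1 loosely, as each person's own time. The double index and the use of t in step 2 make that reading hard to sustain.

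**Conclusion.** The text and code of SAP section 7 specify different estimators. They differ in the time at which the weight is evaluated and in whether it depends on covariates. The text version is not a valid weight for cases before the horizon. Under censoring assumed to match the stated follow-up, it inflates the weighted case total over the own-time total by about 1.2–1.3 fold at 5 years and 1.6–2.4 fold at 9 years. The mismatch itself is certain from the documents; these sizes depend on the assumed curve and horizon.

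AUCs produced by the printed code are free of this particular error. They still rely on the non-informative censoring assumed in SAP section 6.3.1, because G in the code is marginal.

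A reader might also infer that bringing the text into line with the code would repair everything. It would not. Given a marginal G, the missing control weight cancels in AUC, sensitivity and specificity, but it distorts PPV, NPV, precision, F1, accuracy and MCC. Under the uniform censoring curves, the code alone already doubles the 9-year case share (0.43–0.46 against 0.22), and the text rule adds a further factor of about 1.4–1.5 (0.60–0.67). The Weibull, uniform and beta curves show the same pattern, with 0.39–0.41 for the code and 0.53–0.59 for the text rule.

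**What to change.** - In SAP section 7, step 1, define the weight as 1/G(T_i) for a case with event time T_i ≤ t, and as 1/G(t) for a person still under observation after t.
- In the `cum_metrics` code, apply the control weight 1/G(t) to the false-positive and true-negative counts.
- State that G is marginal and fitted in the training set, as the code has it, and remove the conditioning on X_i from the text.
- List the evaluation horizons.
- Confirm which weights produced the reported metrics. Recompute PPV, NPV, precision, F1, accuracy and MCC in any case. Recompute the AUCs only if the written formula was used.

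The cost is one formula, a small code change and a rerun. No new data are needed.

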### **6.3 Cox proportional hazards model**

#### **6.3.1 Censoring and the Assumption of Independence**

In survival data analysis, censoring occurs when an event is not observed due to termination of follow-up, loss to follow-up, or other reasons. To obtain unbiased estimates using Kaplan–Meier curves and Cox models, it is crucial that the censoring mechanism is independent of the actual event occurrence time. In this study, for outcomes other than death, patients censored due to loss to follow-up or the end of the 10-year follow-up period are assumed to be censored non-informatively.

Importantly, since all-cause mortality is included as an event within our composite outcome, deaths are treated as events rather than censoring. To address potential undercounting of events when using single-outcome definitions and to appropriately account for the competing risk of death, we construct a composite outcome that comprises  $\geq 40\%$  decline in eGFR, end-stage kidney disease, long-term dialysis, kidney transplantation, and all-cause mortality.

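### The only censoring weights specified ignore covariates, so they cannot do what the protocol asks of IPCW: account for informative loss to follow-up

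*Combined protocol and SAP*

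**What the plan says.** **Purpose.** Protocol 3.7 lists, among its sensitivity analyses, "inverse-probability-of-censoring weighting (IPCW) to account for informative loss-to-follow-up, computing weights within the training set". SAP 7, Data Preparation, gives a more general instruction: "Apply inverse probability of censoring weights (IPCW) on the test set to adjust for censoring".

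**Formula.** SAP 7 writes the weight as 1/Ŝ(t|X_i). The denominator "is the estimated probability of being uncensored at time" t, conditional on the covariates X_i of subject i.

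**Code.** The evaluation function in SAP 7 opens with "def cum_metrics(survival_train, survival_test, estimate, times, AUC_sfd=False". It receives training outcomes, test outcomes, risk scores and time points. The introduction to SAP 7 lists the same inputs in prose. The censoring estimator comes from a nonparametric module ("from sksurv.nonparametric import CensoringDistributionEstimator, SurvivalFunctionEstimator") and is fitted to the training outcomes only ("cens.fit(survival_train"). In the worked example those outcome arrays hold an event indicator and a time, nothing else. The weight multiplies the case indicator; controls are counted unweighted.

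**Assumption.** SAP 6.3.1 says that people lost to follow-up or reaching 10 years "are assumed to be censored non-informatively".

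**The concern.** A censoring weight removes bias from covariate-related loss only if it varies with the covariates that drive the loss. The formula promises that and the code does not deliver it. Two test-set cases with the same event time get the same weight, whatever their eGFR, UACR or risk score. The weights therefore need the independence assumption that the protocol's sensitivity analysis is meant to relax.

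Time-dependent AUC is a main discrimination measure and a basis for the comparison with KFRE. If the code were used for the sensitivity analysis, agreement with the main result would look like evidence of robustness to informative loss, although that had not been examined.

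**Working it through.** The documents give no figure on this point, so there is none to reproduce. The check has four parts.

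**1. The places side by side**

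| Place | Role of covariates in the censoring weight |
|---|---|
| Protocol 3.7 | Needed: the purpose is informative loss |
| SAP 7, formula | Present: Ŝ(t given X_i) |
| SAP 7, list of function inputs | None beyond outcomes, scores and times |
| SAP 7, code | None: one curve from times and event indicators |
| SAP 6.3.1 | Not needed: loss assumed non-informative |

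No other IPCW specification appears.

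**2. What the coded weights estimate**

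Let G(t|X) be the probability of remaining uncensored to t given X, and G(t) its marginal version. The code gives a case at time T_i ≤ t the weight 1/Ĝ(T_i), and a control (observed time beyond t) the weight 1.

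- A true case with covariates X is observed with probability G(T_i|X). Its expected contribution is G(T_i|X)/G(T_i), which equals 1 for every X only if G(·|X) = G(·).
- A true control is retained with probability G(t|X). If that is the same for everyone, the missing control weight cancels in AUC and specificity. If it varies with X, it does not cancel.

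Covariate-conditional weighting therefore needs 1/G(T_i|X_i) for cases and 1/G(t|X_i) for controls.

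**3. Illustrative size**

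Inputs, all assumed:
- score = X + 0.5Z, with X and Z standard normal;
- event hazard 0.016·exp(score) per year;
- censoring hazard 0.07·exp(γX) per year, with an administrative end at 10 years;
- horizon 8 years; 400,000 people per scenario.

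Here γ is the censoring log hazard ratio per SD of X, the covariate that dominates the score. The simulated event proportion was 12–17% and mean observed time 5.9–6.4 years, near the derivation set's 17.98% and 6.51 years (SAP 3). The conditional column uses the true G(t|X).

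| γ | True AUC | Marginal weights (as coded) | Error | Conditional weights |
|---|---|---|---|---|
| −1.0 | 0.794 | 0.741 | −0.053 | 0.792 |
| −0.5 | 0.794 | 0.767 | −0.027 | 0.795 |
| 0 | 0.791 | 0.791 | 0.000 | 0.791 |
| +0.5 | 0.795 | 0.814 | +0.019 | 0.795 |
| +1.0 | 0.797 | 0.821 | +0.024 | 0.798 |

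A separate run of 200,000 people per scenario, at a 9.9-year horizon and with γ per SD of the score, gave errors of 0.774 − 0.807 = −0.033 (γ = −0.5), 0.789 − 0.807 = −0.018 (−0.3), 0.824 − 0.809 = +0.015 (+0.3) and 0.827 − 0.808 = +0.019 (+0.5). The error changes sign with γ, so it cannot be assumed conservative.

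**4. Comparison with sampling error**

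Supplementary Table 1 gives 171 test-set participants with 32 composite events, hence 139 without. The Hanley–McNeil formula at an assumed AUC of A = 0.81 gives:

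- Q₁ = A/(2 − A) = 0.81/1.19 = 0.681
- Q₂ = 2A²/(1 + A) = 1.312/1.81 = 0.725
- variance = [0.154 + 31(0.681 − 0.656) + 138(0.725 − 0.656)]/(32 × 139) ≈ 0.00234
- SE ≈ 0.048

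A simulation at PMBB size (680 training, 171 test, 8-year horizon, 300 replicates, γ within ±0.5) gave:

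| Quantity | Result |
|---|---|
| Bias of AUC, marginal weights | about −0.025 to +0.016 |
| Test-set SD of AUC | 0.055 to 0.059 |
| Root mean squared error, marginal weights | 0.055 to 0.064 |
| Root mean squared error, fitted eight-covariate censoring model | 0.055 to 0.062 |

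Within ±0.5 the bias is below the sampling error of this test set. At γ = −1.0 it is about the same size.

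**The case against.** **The function may not be the sensitivity analysis.** Informative loss is named only in Protocol 3.7, whereas SAP 7 speaks only of censoring. Marginal weights are coherent with SAP 6.3.1, and the listing is labelled pseudocode, so the executed code may differ. This stands as a limit on what can be said about the final results. It does not remove the mismatch: the SAP's own formula is conditional, its prose list of inputs also omits covariates, and no other IPCW is described.

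**Heavy, covariate-related loss is not shown.** A reader might infer it from mean follow-up of 7.18 out of 10 years, from 7.18 against 7.62 years in high- and low-risk genotypes (Appendix 1, P<0.01), or from 6.67 years at eGFR ≤60 (Appendix 2). The documents do not support this.
- No loss rate is given, and staggered index dates with a common end of study would also shorten follow-up.
- The first contrast is between genotypes, while APRS is evaluated within the high-risk group.
- The 6.67-year group had 21.76% deaths, against 7.29% in the high-risk group with eGFR >60. Death is a composite event, not loss. The genotype contrast within eGFR ≤60 has P = 0.31.

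**ARIC and UK Biobank.** A reader might infer that PMBB censoring weights will be applied to these cohorts, because the function requires training outcomes and Protocol 3.7 ties the weights to the training set. Nothing says so; the point is unspecified.

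**Gain from the fix.** At this test-set size, fitted conditional weights lowered root mean squared error by at most about 0.008, and not at all when higher-risk people were censored more. That stands. The reason for the change is that the analysis should address its stated question, not that precision will improve.

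**Conclusion.** The inconsistency is certain from the text. The protocol's purpose and the SAP's formula require covariate-conditional weights; the only implementation supplied is marginal and weights cases only. As specified, it relaxes nothing beyond the independence that SAP 6.3.1 assumes.

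The size of any bias is unknown. The range of about −0.05 to +0.02 in AUC rests on assumed censoring log hazard ratios of ±0.3 to ±1.0 per SD and exponential event and censoring times. A reader might infer that the reported AUCs are materially biased; the documents do not establish that. The supported conclusion is narrower: the planned sensitivity analysis, as written, could not show whether they are.

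**What to change.** **Preferred**
- Keep the marginal-weight result as the main estimate, and describe those weights as assuming independent censoring.
- Add the sensitivity analysis promised in Protocol 3.7. Fit a censoring model (for example a Cox model for time to censoring) on the baseline covariates already collected and the APRS. Weight cases by 1/G(T_i|X_i) and controls by 1/G(t|X_i). State the truncation rule and report the two results together.
- Use horizons before 10 years. The code counts as controls only people observed beyond the horizon, and follow-up stops at 10 years, so none remain at year 10.
- State which cohort's data estimate the censoring distribution for ARIC and UK Biobank, preferably the cohort being evaluated. Reconcile this with the training-set rule in Protocol 3.7.
- Align Protocol 3.7 and SAP 6.3.1 on whether loss is treated as possibly informative.

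**Alternative**
- Rewrite the SAP 7 formula as marginal weights under independent censoring, and withdraw the informative-loss claim from Protocol 3.7.

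**Cost.** The first route is a small code change with somewhat more variable weights. The second is a text edit, but it leaves robustness to informative loss untested.
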